## Abstract

**Background:**

Indigenous youth in Northwestern Ontario who need mental health supports experience longer waits than non-Indigenous youth within the region and when compared to youth in urban areas. Limited access and extended waits can exacerbate symptoms, prolong distress, and increase risk for adverse outcomes. Innovative approaches are urgently needed to provide support for Indigenous youth in Northwestern Ontario. Using a randomized controlled trial design, the primary objective of this study is to determine the effectiveness of the JoyPop app compared to usual practice (UP; monitoring) in improving emotion regulation among Indigenous youth (12–17 years) who are awaiting mental health services. The secondary objectives are to (1) assess change in mental health difficulties and treatment readiness between youth in each condition to better understand the app’s broader impact as a waitlist tool and (2) conduct an economic analysis to determine whether receiving the app while waiting for mental health services reduces other health service use and associated costs.

**Methods:**

A pragmatic, parallel arm randomized controlled superiority trial will be used. Participants will be randomly allocated in a 1:1 ratio to the control (UP) or intervention (UP + JoyPop) condition. Stratified block randomization will be used to randomly assign participants to each condition. All participants will be monitored through existing waitlist practices, which involve regular phone calls to check in and assess functioning. Participants in the intervention condition will receive access to the JoyPop app for 4 weeks and will be asked to use it at least twice daily. All participants will be asked to complete outcome measures at baseline, after 2 weeks, and after 4 weeks.

**Discussion:**

This trial will evaluate the effectiveness of the JoyPop app as a tool to support Indigenous youth waiting for mental health services. Should findings show that using the JoyPop app is beneficial, there may be support from partners and other organizations to integrate it into usual care pathways.

**Trial registration:**

https://clinicaltrials.gov/study/NCT05898516 [registered on June 1, 2023].

## Administrative information

Note: the numbers in curly brackets in this protocol refer to SPIRIT checklist item numbers. The order of the items has been modified to group similar items (see http://www.equator-network.org/reporting-guidelines/spirit-2013-statement-defining-standard-protocol-items-for-clinical-trials/).

## Introduction

### Background and rationale {6a}

Northwestern Ontario, Canada, is situated within the Nishnawbe Aski Nation and is home to 49 Indigenous communities. Indigenous youth within this region, and generally, are exposed to circumstances that increase their risk for mental health difficulties including histories of family residential school attendance [1], early childhood adversity [2], and economic and housing instability [3]. As a result, Indigenous youth experience more mental health difficulties than non-Indigenous youth [4]. Indigenous youth within Northwestern Ontario experience longer waits for mental health services when compared to non-Indigenous youth within the region and in other areas of the country [5–7]. These issues are concerning as extended time on waitlists can exacerbate symptoms, prolong distress, and increase risk for more adverse outcomes [8–11]. Delayed access to mental health services also negatively impacts treatment engagement [9, 12], with non-attendance, decreased motivation, and reduced satisfaction with services frequently reported following prolonged wait times [9, 11].

Innovative approaches are urgently needed to provide support for Indigenous youth. Making use of emerging technologies (e.g., mobile health apps) to provide mental health supports is discussed as holding particular promise for youth, for those living in rural and remote areas, and for Indigenous people [13, 14]. With these “just-in-time” interventions [15], support can be accessed in-the-moment, when it is needed most [16]. However, despite their potential, significant gaps exist between the growing number of apps available in the public domain and empirical demonstration of the beneficial impacts of apps for users [17–19]. For example, a recent review found that only 3.4% of available mobile mental health apps had research to support the claims made about their effectiveness [20]. More studies on the effectiveness of youth-oriented mobile mental health apps among Indigenous youth are especially needed before providers adopt or integrate them into usual care pathways [21].

This research is developed in partnership with an Indigenous-led community organization that is guided by Anishinabek culture and which supports Indigenous children, families, and communities within Northwestern Ontario. Our team is evaluating the impact of a mobile mental health app (JoyPop; see Fig. 1) as a tool for Indigenous youth waiting for mental health services. While using an app is unlikely to alleviate all mental health difficulties among youth seeking services, it could serve as a skill-building tool that improves emotion regulation, reduces mental health symptoms, and increases motivation prior to treatment, thus contributing to a better treatment response [11, 22, 23].

**Fig. 1 Fig1:**
[figure not shown]
The JoyPop app

The JoyPop app was developed using patient-oriented research methods involving active collaboration between youth, service providers, and clinician-scientists [24]. The app incorporates evidence-based features that support improved emotion regulation [25]. JoyPop’s focus on emotion regulation reflects current recommendations for mental health interventions to focus on transdiagnostic factors rather than addressing individual disorders in isolation [26] and has relevance to Indigenous youth in Northwestern Ontario who typically present with difficulties related to emotion regulation [27].

The JoyPop app has a growing evidence base that shows important benefits or potential for youth [25]. MacIsaac et al. examined the impact of the JoyPop app among older youth in university [25] and found that with each day of app use, there was a corresponding positive change in emotion regulation and mental health [25]. Improvements were especially evident for those with more childhood adversity (e.g., abuse, neglect). [name] et al. examined feedback from university students who used the app for up to 4 weeks [28] and found that most students described experiencing positive outcomes (e.g., improved emotional expression) after using the app. Kim et al. gathered input from Indigenous community members and stakeholders and found that most saw potential for the app to foster resilience among youth [29]. Finally, Malik et al. evaluated the acceptance of the app among youth (12–18 years) receiving mental health services and among service providers, both in Northwestern Ontario [30]. Youth and service providers perceived the app as useful because it facilitated accessibility to coping skills. All participants expressed positive attitudes and feelings towards the app because of the benefits it provided youth or the advantages it could provide to local mental health services.

### Objectives {7}

The primary objective of this study is to determine the effectiveness of the JoyPop app compared to usual practice (UP; monitoring) in improving emotion regulation among Indigenous youth (12–17 years) awaiting mental health services. Based on our past research [25, 28], we hypothesize that youth receiving the app will show significantly greater improvement in emotion regulation compared to youth receiving only UP.

The secondary objectives are to (1) compare change in mental health difficulties and treatment readiness between youth in each condition to better understand the app’s broader impact as a waitlist tool and (2) conduct an economic analysis to determine whether receiving the app while waiting for mental health services reduces other health service use and associated costs.

### Trial design {8}

A pragmatic, parallel arm randomized controlled superiority trial will be used. Participants will be randomly allocated in a 1:1 ratio to the control (usual practice; UP) or intervention (UP + JoyPop) condition. Stratified block randomization will be used to randomly assign participants to each condition. All participants will be monitored through existing waitlist management practices, which involve regular phone calls to check in and assess functioning. Participants in the intervention condition will receive access to the JoyPop app for 4 weeks and be asked to use it at least twice daily. All participants will be asked to complete primary (emotion regulation) and secondary (mental health symptoms, treatment readiness, service utilization) outcome measures at pre (baseline), mid (after 2 weeks), and post (after 4 weeks) timepoints.

The Standard Protocol Items: Recommendations for Intervention Trials (SPIRIT) guidelines are being followed. The trial was registered with ClinicalTrials.gov (NCT05898516). All procedures have been reviewed and approved by the Research Ethics Board at the Thunder Bay Regional Health Sciences Centre (acting as the Board of Record for Lakehead University clinical research projects) and the Research Advisory Committee at our partner organization, Dilico Anishinabek Family Care (“Dilico”).

## Methods: participants, interventions, and outcomes

### Study setting {9}

Youth on the waitlist for mental health services at Dilico, located in Northwestern Ontario, Canada, will be recruited. Data collection will occur at Dilico. Dilico provides a range of responsive individual, family, and community programs and services for the complete life journey of Anishinabek people. Dilico is a self-governed organization that is recognized as a leader in research and delivery of child welfare, mental health and addictions, and health services. The community-based services delivered by Dilico are designed to enhance the well-being of Anishinabek children, families, and communities in a culturally safe manner [31].

### Eligibility criteria {10}

Youth are eligible if they are on the waitlist for mental health services with Dilico and are between 12 and 17 years old. If participants cannot attend a session at Dilico (e.g., due to weather), accommodations will be offered (e.g., to hold the session virtually).

### Who will take informed consent? {26a}

Interested participants will attend an orientation session at Dilico. During the session, a research assistant will present information about the study and provide a copy of an information letter that contains all relevant details. Each potential participant will have time to review the information letter and ask questions. Participants will then be provided with the informed consent form to review and complete. Potential participants are deemed capable of providing consent independently. For youth under 16 years, the research assistant will encourage youth of the desirability of informing their parent(s)/caregiver(s) about their involvement in the research; however, parental/caregiver involvement/consent is not required. This approach is consistent with the Canadian Tri-Council Policy Statement: Ethical Conduct for Research Involving Humans [32], with the practices in place at Dilico Anishinabek Family Care, and with youth 12 years old and up being able to consent to counseling services independently via the provincial Child, Youth and Family Services Act [33].

### Additional consent provisions for collection and use of participant data and biological specimens {26b}

No additional consent provisions are in place. No biological samples will be collected.

## Interventions

### Explanation for the choice of comparators {6b}

The control condition (UP) was chosen to account for the potential effects of time on emotion regulation. It will be used to test whether receiving the JoyPop app is associated with improved outcomes compared to UP.

### Intervention description {11a}

The control condition (UP) involves participants being monitored through existing waitlist management practices in place at Dilico (i.e., regular phone calls to check in and assess functioning). The intervention condition (UP + JoyPop) involves participants being monitored through existing waitlist management practices in place at Dilico plus receiving access to the JoyPop app. The app is currently only available for iOS devices (iPad, iPhone, iPod). If participants do not have access to their own iOS device, they will be provided with a refurbished iPhone for the duration of the study. The refurbished iPhones contain only the JoyPop app (no other features available/enabled). Participants in the intervention condition will be asked to use the app at least twice daily for 4 weeks but will otherwise not be provided with requirements related to app usage. The app incorporates evidence-based features that support improved emotion regulation [25] including Rate My Mood, Journaling, Breathing Exercises, Art, SquareMoves, SleepEase Circle of Trust, and Call for Help (see Fig. 1 for description of features).

### Criteria for discontinuing or modifying allocated interventions {11b}

Any participant can request to discontinue the intervention by contacting the research team. At baseline, participants will not only complete outcome measures but will also complete a demographics measure and psychiatric symptoms screening measure. These measures will be used to describe the sample and better understand who is accessing the research study. If a participant endorses recent suicidal thoughts on the symptoms screening measure, the research assistant will notify the clinical services case manager from Dilico who will identify a counselor to conduct a suicide risk assessment with the participant and provide any necessary immediate supports. The participant and counselor will determine whether continuing with the study is recommended. There are no pre-determined criteria that would require a participant to discontinue the allocated intervention.

### Strategies to improve adherence to interventions {11c}

Our pilot research showed that having in-person contact with a consistent research assistant was important for participant engagement [34]. Therefore, all participants in this study will meet with a research assistant when they attend an orientation session at the beginning of the study. Participants in the intervention condition will receive text and email reminders to use the app each day. Text and email reminders will be automated to arrive each day at 8 am and 8 pm. Participants in both conditions will also receive text and email reminders to attend sessions to complete pre, mid, and post outcome measures. Participants will receive cash compensation for each session that they attend ($20 baseline; $25 mid; $30 post) and an additional cash incentive ($25) if they attend all three sessions. All participants will be encouraged to reach out to the research team with any questions or concerns throughout the study.

### Relevant concomitant care permitted or prohibited during the trial {11d}

Participants are permitted to receive concomitant care as needed. No concomitant care and interventions are prohibited during the trial. Concomitant care will be assessed through the outcome measures completed by participants.

### Provisions for post-trial care {30}

All participants remain on the waitlist for services with Dilico; thus, most will likely receive care post-intervention (unless they choose not to once services are offered). There are no expected trial-related harms.

### Outcomes {12}

#### Primary outcomes

The primary outcome is change in emotion regulation skills from pre (baseline) to mid (after 2 weeks) and post (after 4 weeks). Emotion regulation will be assessed with the Difficulties in Emotion Regulation Scale—Short Form (DERS-SF) [35, 36]. The DERS-SF is 18 items and asks respondent how often specific statements applied to them over the previous 2 weeks on a 5-point scale ranging from 1 (*almost never*) to 5 (*almost always*). We will examine change in overall emotion regulation via the total DERS-SF score and change in specific domains via the DERS-SF subscales. Total scores range from 18 to 90 with higher scores indicating greater difficulties in emotion regulation. Subscales are as follows: strategies (e.g., “When I was upset, I believed there was nothing I could have done to make myself feel better”), non-acceptance (e.g., “When I was upset, I became irritated with myself for feeling that way”), impulse (e.g., “When I was upset, I became out of control”), goals (e.g., “When I was upset, I had difficulty getting work done”), awareness (e.g., “I paid attention to how I feel”), and clarity (e.g., “I had no idea how I was feeling”). Total subscale scores range from 3 to 15 with higher scores indicating greater difficulty.

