### Participant timeline {13}

### Sample size {14}

Our past research suggests a medium effect for the primary outcome [43]. We estimated conservatively in calculating sample size, using *f* = 0.2 (small to medium effect), alpha = 0.05, and power = 0.95 for a 2 (between subjects; treatment condition) by 3 (within subjects; time) mixed design, which approximates the statistical power needed for the planned linear mixed model under the assumption of compound symmetry (i.e., homogeneity of variance and covariance) [44]. Results suggested a sample size of 66 would achieve necessary power. Given our pilot data [34], we estimate 60% retention throughout the study (40% attrition), meaning we will need an initial sample size of 110.

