## Statistical methods

### Statistical methods for primary and secondary outcomes {20a}

An independent, contracted, statistician will lead the analyses. Linear mixed modeling will be used to test hypotheses related to emotion regulation, mental health symptoms, and treatment motivation. Polynomial contrasts will be used to test for linear and quadratic changes over time. Effect sizes will be calculated using the Cohen’s *d* formula adapted by Feingold [51]. In the economic analysis, mental health services utilization and their costs during the 4-week period among participants in each condition will be estimated. Then, the incremental costs/savings associated with receiving the app using a cost-consequence analysis will be estimated [52].

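### Seven DERS-SF scores at two follow-ups are all listed as primary, with linear and quadratic contrasts, and none is named as decisive, although the sample size rests on one test at 0.05

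*Protocol article*

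**What the plan says.** All places are in the protocol article.

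- **Primary outcomes (item 12), visits:** "The primary outcome is change in emotion regulation skills from pre (baseline) to mid (after 2 weeks) and post (after 4 weeks"). Neither follow-up is singled out.
- **Primary outcomes, scores:** "We will examine change in overall emotion regulation via the total DERS-SF score and change in specific domains via the DERS-SF subscales". Six subscales are then listed, so with the total there are seven scores in the primary tier. Secondary outcomes and exploratory measures have their own separate headings.
- **Statistical methods (item 20a):** linear mixed models test the hypotheses, and "Polynomial contrasts will be used to test for linear and quadratic changes over time".
- **Objectives (item 7):** one hypothesis, that youth given the app improve significantly more in emotion regulation than youth on usual practice. It names no score, visit or contrast.
- **Sample size (item 14):** "alpha = 0.05, and power = 0.95 for a 2 (between subjects; treatment condition) by 3 (within subjects; time) mixed design", giving 66, raised to 110 for 40% attrition. This is the only place where an alpha appears.

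**The concern.** The hypothesis is singular, but the primary tier is plural. As written, the hypothesis could be called supported by the total or any subscale, at week 2 or week 4, or on a linear or a quadratic contrast. The more of these routes are open, the further the chance of a false claim rises above the 5% for which the trial was sized.

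The quadratic contrast adds a problem of meaning. With visits at 0, 2 and 4 weeks the linear weights are (-1, 0, 1), which is the week-4 change. The quadratic weights are (1, -2, 1), which set week 2 against the average of baseline and week 4. A difference between conditions that appears at week 2 and has gone by week 4 can make the quadratic term significant, yet it is weak evidence of an app effect that lasts through the four weeks.

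At stake is whether a result on one subscale, or at week 2 only, could be reported as meeting the primary outcome.

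**Working it through.** **1. Reproduce the plan's sample size.** Stated inputs: f = 0.2, alpha 0.05, power 0.95, two groups, m = 3 visits, compound symmetry. The correlation between visits is not stated; 0.5 is assumed.

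For the condition-by-time interaction, lambda = f² × N × m / (1 - rho), with 2 and 2(N - 2) degrees of freedom.

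- N = 66: lambda = 0.04 × 66 × 3 / 0.5 = 15.84; df 2 and 128; critical F 3.07; power 95.0%.
- N = 64: power 94.4%.
- Attrition: 66 / 0.60 = 110.

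So 66 and 110 are reproduced as one 2-df interaction test on one score. Assumed correlations of 0.3 and 0.7 would give 92 and 42, and a between-group main effect at 0.5 would give 220. None of these matches.

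**2. Count the candidate results.** There is one total and six subscales, so seven scores. Each can have a linear and a quadratic contrast, so 14 tests. The two follow-up changes span the same two degrees of freedom as the two contrasts, so the count is 14 and not 28.

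**3. Independence as a reference.** 1 - 0.95^7 = 30.2% and 1 - 0.95^14 = 51.2%. These overstate the risk, because the total is the sum of the subscales.

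**4. Allow for dependence.** The simulation assumes no effect, six equally variable subscales with common correlation r, the total as their sum, and linear and quadratic contrasts that are independent (as they are under compound symmetry). The protocol gives no subscale correlations, so r is an assumption shown as a range. The entries are the chance of at least one two-sided p < 0.05:

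| r | 7 scores, one test each | 7 scores, both contrasts |
|---|---|---|
| 0 | 28% | 48 to 49% |
| 0.4 | 23% | 40 to 41% |
| 0.5 | 21% | 37 to 38% |
| 0.6 | 19% | 34% |
| 0.8 | 14% | 26% |

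Paired figures come from two simulations, one with 66 participants and t tests and one with normal test statistics.

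- Testing the week-2 and week-4 changes in place of the two contrasts gives 46% down to 24%.
- Counting only results in the app's favour gives about 7 to 15% for seven linear tests and about 13 to 28% for 14 tests.
- The total alone with both contrasts gives 1 - 0.95² = 9.75%.
- The total alone with one test gives about 5%.

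**5. Effect of each remedy on the sample size.**

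- One test on the total, 2-df interaction: power 95.0% at 66, as planned.
- One test on the total, linear (week-4) contrast: with the same lambda of 15.84 on 1 df, power is about 97% if the whole effect is linear.
- All seven scores kept co-primary at 0.05/7: power at 66 is about 82%. Power of 95% needs 94 completers, and 94 / 0.60 rounds up to 157 randomised.
- All 14 tests at 0.05/14: power is about 75%, and 102 completers are needed, 102 / 0.60 = 170 randomised.

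The last two apply the 2-df test at the lower alpha and are approximate.

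**The case against.** The strongest reply is that the article supports a narrower reading. It speaks of the primary outcome in the singular, ties overall emotion regulation to the total score, and states a hypothesis about emotion regulation as a whole. It uses similar total-and-subscale wording for the DASS-21 and SDQ, so the sentence may only describe the instrument. The sample size fits one interaction test on one score, for which the error is 5%. Multiplicity methods are commonly left to an analysis plan, which is not shown here.

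Part of this stands. Three stronger readings are tempting, and the document does not support them:

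- A reader might infer that any one of 14 results wins, each at an unadjusted 0.05. The article states neither the rule nor the lack of adjustment, so the error rates above are conditional on such a rule.
- A reader might state the false-success rate flatly as 30 to 50%. Those are the independence figures for 7 and 14 tests. Once dependence is allowed for, one test per score gives 14 to 28%, and false results in the app's favour are about half as frequent.
- A reader might conclude that the contrasts test change over time and not the difference between conditions. The methods section says the models test the hypotheses, and the primary hypothesis is a between-condition one. One condensed sentence does not show that the comparison is missing.

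What does not stand is the appeal to an unseen analysis plan. Fixing the primary outcome is the protocol's task. This protocol has secondary and exploratory tiers and still places the subscales and both visits in the primary one. A plan that demoted them would be changing the protocol, not completing it. Calling the total overall suggests a lead score but does not make it decisive.

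**Conclusion.** The point holds in a conditional form. The primary tier contains seven scores at two follow-ups, analysed with two contrasts, and nothing says which result decides the trial, while the sample size is for one test at 0.05. If any of these results could be claimed, the two-sided error is about 14 to 28% (one test per score) or about 26 to 49% (both contrasts), and about half that in the app's favour. Even with the total alone, leaving both contrasts open doubles the error to about 10%. The figures rest on assumed subscale correlations of 0 to 0.8, and the reproduction of 66 rests on an assumed between-visit correlation of 0.5. If the total with a single condition-by-time test is what the investigators intend, the error is 5% and only the wording needs to say so.

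**What to change.** - Name the DERS-SF total as the only primary score.
- Name one decisive condition-by-time test at two-sided 0.05: either the 2-df interaction that was sized, or the week-4 (linear) contrast. Both hold 5%. Choose and date the choice before the data are analysed.
- Move the six subscales and the quadratic contrast to secondary or supportive status, and the week-2 difference too as a separate comparison. Use Holm adjustment or report confidence intervals only.
- State that effectiveness is concluded from the primary test alone.

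The cost is a change of wording in the protocol and any analysis plan, and a registry update if the entry there carries the same plural outcome. The sample size stays at 66 completers and 110 randomised. The small downside is that a subscale-only or week-2-only result can no longer be called a primary success.
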